## Abstract

**Background:**

Intensive care unit–acquired weakness (ICU-AW) research focuses predominantly on intrinsic muscle pathology rather than integrated systemic interactions, which are commonly studied in exercise science. Peak oxygen uptake ($\dot{V}O_{2peak}$), $\dot{V}O_{2}$ on/off kinetics, and skeletal muscle oxygenation provide a quantitative evaluation of exercise capacity and are infrequently measured in intensive care unit (ICU) survivors. Routine cardiopulmonary exercise test (CPET) research separates $\dot{V}O_{2peak}$ and $\dot{V}O_{2}$ kinetics assessments into multiple sessions. Yet, a combined experimental approach may enhance diagnosis, follow-up retention, and mechanistic insight for patients with ICU-AW.

**Objective:**

This prospective cross-sectional observational study aims to develop a standardized, single-session CPET protocol for combined assessment of $\dot{V}O_{2peak}$, $\dot{V}O_{2}$ kinetics, and skeletal muscle microvascular oxygenation in ICU survivors, enabling quantitative and integrated assessment of ICU-AW.

**Methods:**

Adults mechanically ventilated for ≥7 days will be recruited to participate 6 months post-ICU discharge in a modified CPET exercise session on an upright cycle ergometer. The proposed standardization will involve (1) the estimation of $\dot{V}O_{2peak}$ using a priori formulas with a $\dot{V}O_{2peak}$ correction factor for the ICU population, (2) $\dot{V}O_{2}$ on-kinetics (constant work rate) targeting relative 30% $\dot{V}O_{2reserve}$, (3) an incremental ramp exercise based on self-reported functional status, and (4) a 10-minute recovery to quantify $\dot{V}O_{2}$ off-kinetics. In addition, near-infrared spectroscopy will be placed on the vastus lateralis muscle to simultaneously collect tissue saturation index and deoxyhemoglobin during each phase of the protocol.

**Results:**

Recruitment is anticipated to begin in June 2026 and is expected to be completed in 2029/2030. The anticipated sample size will be approximately 48 participants based on the feasibility of recruiting 1 participant per month and a sample size calculation based on Bland-Altman limits of agreement between predicted and measured $\dot{V}O_{2peak}$.

**Conclusions:**

The intensive care unit combined assessment of cardiorespiratory exercise (ICU-CARE) CPET protocol will enable the quantitative evaluation of $\dot{V}O_{2peak}$, $\dot{V}O_{2}$ on/off kinetics, and local microvascular skeletal muscle oxygenation during a single exercise session, facilitating the integrated physiological study of ICU-AW.

## Introduction

Intensive care unit–acquired weakness (ICU-AW)—defined as skeletal muscle and motor nerve dysfunction during and after critical illness [1]—remains a substantial contributor to long-term morbidity and loss of independence after prolonged intensive care unit (ICU) admission [2,3], occurring in 25% to 75% of mechanically ventilated patients [1,4]. Despite a high prevalence, there are currently limited tools to accurately quantify this disease burden and limited interventions to rehabilitate skeletal muscle after ICU discharge. The current approach for studying ICU-AW focuses on the pathological changes within the muscle [5], with minimal consideration for its in vivo physiological environment [6]. However, isolated skeletal muscle research may overlook the complex and integrated physiological systems contributing to ICU-AW. In addition, there is a paucity of research to describe the link between cardiovascular/respiratory dysfunction and ICU-AW, including how impairments lead to reduced exercise capacity and poor health outcomes.

The cardiopulmonary exercise test (CPET) is used clinically and in research to assess aerobic fitness and exercise capacity, predict health outcomes, diagnose cardiopulmonary dysfunction and functional limitations, and evaluate response to interventions [7]. The most common exercise metric for CPET is peak oxygen uptake $(\dot{V}O_{2peak}$), defined as the highest $\dot{V}O_{2}$ achieved during a test [8], particularly until the limit of tolerance (or willingness), signifying exercise capacity within this protocol. For many healthy and diseased populations, $\dot{V}O_{2peak}$ is a robust and comprehensive evaluation of global cardiovascular fitness and a strong predictor of mortality [9-11]. Additionally, $\dot{V}O_{2}$ kinetics assess the integrated capacity of the O_2_ transport pathway [12]. $\dot{V}O_{2}$ on-kinetics refers to the exponential rise of $\dot{V}O_{2}$ toward a steady state from rest to exercise below the lactate threshold, where the slope of the exponential rise represents the rate at which oxidative phosphorylation adjusts to a sudden increase in energy demand at a constant workload, reflecting both systemic oxygen transport and muscle metabolism [13]. $\dot{V}O_{2}$ off-kinetics refers to the exponential decline of $\dot{V}O_{2}$ postexercise [12], representing the rate of metabolic recovery, where oxygen uptake returns to baseline levels. Moreover, faster $\dot{V}O_{2}$ kinetics constitutes a small O_2_ deficit, less substrate-level phosphorylation, and greater exercise tolerance, whereas slower $\dot{V}O_{2}$ kinetics is linked to a higher O_2_ deficit, presenting a greater challenge to homeostasis, and is associated with poor exercise tolerance [12]. Quantification of these 3 variables—$\dot{V}O_{2}$_peak_, $\dot{V}O_{2}$ on- and off-kinetics—is critical to understanding the interplay between cardiopulmonary and muscular physiological mechanisms [13,14]. Together, they contribute to the overall phenotype of aerobic fitness, exercise efficiency, and exertional tolerance that impact quality of life and overall survival [13,15-17].

Research suggests that pathological conditions that affect cardiopulmonary function and muscle metabolic capacity are expected to alter $\dot{V}O_{2}$ kinetics [13]. Impediments at any upstream component along the oxygen delivery pathway (eg, lungs, cardiac, vascular, and microvascular) can attenuate $\dot{V}O_{2}$ kinetics, impairing exercise performance and impacting exercise tolerance [7,12,18,19]. While commonly used in clinical and research settings for evaluation of chronic cardiorespiratory diseases such as congestive heart failure, chronic obstructive pulmonary disease, or pretransplantation [20], CPET has not been widely adopted for assessment of ICU survivors after discharge. Past CPET studies in ICU survivors report reduced exercise capacity and limited aerobic fitness [5,7,21-24], yet underlying mechanisms for these findings, particularly beyond skeletal muscle biology, remain underexplored. Moreover, the evaluation of skeletal muscle microvascular oxygenation using near-infrared spectroscopy (NIRS) [25,26] has been notably lacking as a critical gap in our mechanistic understanding of ICU-AW. Overall, the paucity of quantitative and systematic data evaluating exercise capacity in ICU survivors is a key barrier to both understanding the pathophysiology underlying ICU-AW and to tailoring effective patient-centered rehabilitation strategies moving forward.

Typically, evaluation of $\dot{V}O_{2peak}$ and $\dot{V}O_{2}$ on/off kinetics requires multiple exercise sessions in order to first determine participant-specific $\dot{V}O_{2peak}$ and then to use these values to derive a constant work rate (CWR) as a percentage of $\dot{V}O_{2peak}$ or ventilatory thresholds [27-30]. However, this approach can limit recruitment and compliance, and is especially problematic for clinical research with vulnerable or disadvantaged participant groups [31]. Moreover, caregivers of ICU survivors are known to experience depressive symptoms for at least 1 year following discharge [32], which may also impact participation due to the inability or unwillingness to arrange and/or accompany to multiple sessions. Crucially, designing an efficient and simple protocol is critical for both the survivor and caregiver to foster recruitment and compliance. When $\dot{V}O_{2peak}$ and $\dot{V}O_{2}$ on/off kinetics are evaluated in a single session, as has been done by previous researchers [7,14,33], a uniform CWR is often prescribed regardless of fitness level and many times based on subjective parameters, which prevents accurate data comparison between participants. Furthermore, the timing of the phases of the exercise (ie, CWR, ramp, and recovery) within a single session protocol requires standardization, considering relatively short CWR or the implementation of an active recovery, which may compromise data quality for evaluating on/off kinetics [7,28].

Our team has recently developed a single-session CPET protocol for a combined assessment of $\dot{V}O_{2peak}$ and $\dot{V}O_{2}$ on/off kinetics in healthy young adults [28]. In this study, we showed that CWR intensity can be estimated a priori [16] from a Hansen-Wasserman population-based formulae of $\dot{V}O_{2peak}$ (mL kg^−1^ min^−1^), recommended by the American Thoracic Society (ATS) and the American College of Chest Physicians (ACCP) committee [17], relative to sex, body mass, measured $\dot{V}O_{2rest}$ (mL kg^−1^ min^−1^), multiplied by a desired intensity of 30 % $\dot{V}O_{2reserve}$. The estimated $\dot{V}O_{2peak}$ was in good agreement compared to real values measured later in the CPET, where participants achieved steady state (SS $\dot{V}O_{2}$) and adequate return to baseline during the CWR and recovery phases of the protocol.

We believe that this systematic methodological approach will be advantageous for studying exercise physiology in ICU survivors. The intensive care unit combined assessment of cardiorespiratory exercise (ICU-CARE) CPET protocol seeks to evaluate $\dot{V}O_{2peak}$, $\dot{V}O_{2}$ on/off-kinetics, and skeletal muscle oxygenation in ICU survivors. Our objective is to adapt our standardized, single-session CPET to ICU survivors, with the incorporation of skeletal muscle NIRS to better understand how systemic cardiovascular, respiratory, and skeletal muscle microvascular dysfunction contributes to ICU-AW. We hypothesize that this standardized single-session ICU-CARE CPET protocol is (1) feasible for recruitment and completion by ICU survivors and (2) suitable for standardized quantitative measurements of $\dot{V}O_{2peak}$, $\dot{V}O_{2}$ on/off kinetics, and skeletal muscle microvascular oxygenation. These results will enable comparison of exercise capacity, exercise tolerance, cardiorespiratory fitness, cardiopulmonary dysfunctions, and functional limitations between ICU survivors and healthy controls, and assess and track rehabilitation longitudinally after ICU discharge.

## Methods

### Ethical Considerations

This study was approved by the University of Manitoba Health and Institutional Research Ethics Boards (HS25592, SH2022-187, and RRC 2023/2119) and registered in ClinicalTrials.gov under the clinical study ID NCT06193980 (initial release 12/08/2023; last updated 06/11/2026). Written informed consent will be obtained on the day of the exercise testing by all participants.

### Study Design

The ICU-CARE CPET is a prospective cross-sectional observational study that will adhere to the STROBE (Strengthening the Reporting of Observational Studies in Epidemiology) guidelines [34] for final reporting of findings. This study follows the SPIRIT (Standard Protocol Items: Recommendations for Interventional Trials) statement [35], adapted for the purposes of an observational study.

The primary outcome for the study will be the feasibility of recruitment and completion of the protocol. Secondary outcomes of the study will be validation of the a priori equations used in the exercise protocol to calculate $\dot{V}O_{2peak}$ for the ICU population, and physiological observations derived from the study.

### Patient and Public Engagement

We have engaged with an ICU survivor, [name], as a member of our research team, who participated in research design to ensure our project is inclusive and aligns with lived experiences of critical illness. Specifically, we sought consultation on the importance of fitness as a long-term outcome that was given high priority for recovery after critical illness. Furthermore, [name] provided guidance on the accommodations that would be necessary for accessible research within the first 12 months following ICU discharge. We have also reviewed the protocol with [name] to ascertain his perceived capacity to undertake this study during the 12 months after his own ICU discharge. Moving forward, as participants are enrolled in the study, we plan to liaise with them and our identified patient partner in order to refine our experimental protocol and workflow.

### Study Settings

Data will be collected during a single visit to the Pulmonary Function Lab at Winnipeg Health Sciences Centre or St. Boniface Hospital in Winnipeg, Manitoba, Canada. Both sites have equivalent equipment for testing; the option for adding study sites is possible in the future, provided equipment and protocol harmonization. The flowchart for recruitment and evaluation prior to ICU-CARE CPET can be found in Figure 1.

**Figure 1. F1:**
[figure not shown]
Flowchart for ICU-CARE CPET evaluation. ATT: adipose tissue thickness; CFS: Clinical Frailty Scale; CPET: cardiopulmonary exercise test; CWR: constant work rate; DBP: diastolic blood pressure; ECG: electrocardiogram; FI: Frailty Index; FIM: Functional Independence Measure; ICU: intensive care unit; ICU-CARE: intensive care unit combined assessment of cardiorespiratory exercise; MC: metabolic cart; MRC-SS: Medical Research Council sum score; NIRS: near-infrared spectroscopy; SBP: systolic blood pressure. Created in BioRender.

### Inclusion and Exclusion Criteria

Participants will be patients of both sexes (18+ years) who have been mechanically ventilated for ≥7 days, consistent with the prior threshold for the development of ICU-AW [36], who voluntarily agree to participate, and have answered the self-reported functional ability questionnaire. Exclusion criteria will be defined as follows: those who self-report that they cannot climb at least one flight of stairs due to limited exercise capacity, have significant orthopedic or musculoskeletal impairment affecting mobility, have a medical history of neuromuscular disease, have ongoing respiratory limitations (ie, supplemental oxygen), have significant heart disease (ie, ejection fraction less than 30%, unstable ischemic heart disease, and severe valvular heart disease), have a BMI of ≥40 kg/m^2^ (impacting NIRS signal due to adipose tissue thickness) [37], or if the participant’s primary residence is a significant distance from the research center.

### Recruitment Strategy

Before ICU discharge, researchers will screen potential participants for willingness to join follow-up, meeting the inclusion criteria. After 3 months post-ICU discharge, participants will be contacted through telecommunication to determine their ongoing willingness and ability to participate in the ICU-CARE CPET study, with transportation compensation provided within the city limits. Participants will receive detailed information regarding procedures and potential risks before agreeing to attend (please refer to the Pre-CPET Evaluation section below). Due to the high degree of functional impairment and inherently dynamic transitions in care after ICU discharge, we intend for initial participation in the ICU-CARE CPET study to occur at 6 months after ICU discharge, with a range of ±1 month. Participants’ electronic medical records and telephone conversations will be screened for relevant hospital and postdischarge information regarding length of ICU stay, readmission(s), intubation period, concurrent illness, list of medications, and to acquire a recent blood test if available. Participants will then be asked, “How many floors can you walk up quickly without stopping?,” to prescribe the Watt/min increment for the ramp portion of the test (please see Incremental Phase below for more details). Participants will be given an option to be tested again at 12 months after ICU discharge to track their recovery, but this is not required for the main purpose of the study design.

### Pretest Instructions

To ensure data accuracy, participants should adhere to specific pretest instructions through telecommunications leading up to the session, including wearing athletic clothing such as a loose-fitting T-shirt, shorts, and running shoes; avoiding eating, drinking, or smoking within 2 hours before the test; avoiding alcohol consumption and strenuous exercise 24 hours prior to the appointment; avoiding makeup and lotions; and maintaining regular sleep and dietary patterns the day before the test.

### Pre-CPET Evaluation

All potential risks of the procedure will be restated prior to starting the session, and written informed consent will be obtained on the day of the CPET test. According to the ATS, exercise testing is very safe with minimal risk (<0.1%) of cardiac event, and extremely low risk (<0.01%) of death [17]. CPET is routinely undertaken for patients with advanced cardiorespiratory disease, those being evaluated for heart [38] and lung transplantation [39], in advanced heart failure management [40], and in ICU follow-up within the same time period as proposed in this study [5,7,24,41].

Resting systolic (SBP_rest_) and diastolic (DBP_rest_) blood pressure and heart rate (HR_rest_) will be measured prior to exercise, following ATS/ACCP guidelines [17]. ICU-AW will be assessed using the manual testing of muscle strength and severity using the Medical Research Council sum score (MRC-SS) [42], a tool commonly used to diagnose and track the development of ICU-AW [43,44], and the Functional Independence Measure (FIM) questionnaire to assess their ability to carry out activities of daily living [36,45]. FIM score—even early after ICU discharge—has been shown to predict long-term disability in a cohort of ICU survivors [36]. The researchers will also administer the Clinical Frailty Scale, a simple clinician-based tool to quickly evaluate the overall frailty score based on a 9-point scale, and the Frailty Index, which offers a detailed, multidimensional assessment of specific deficits in health and function—both previously validated in the critically ill population [46,47]. Spirometry will be performed prior to beginning the CPET exercise protocol.

### Equipment

The ICU-CARE CPET protocol will be performed using an upright cycle ergometer (Lode Corival | CPET, Lode BV Medical Technology). The pulmonary oxygen uptake ($\dot{V}O_{2}$), carbon dioxide production ($\dot{V}{CO}_{2}$), and the respiratory exchange ratio of $\dot{V}{CO}_{2}$/$\dot{V}O_{2}$ will be collected, monitored, and reported mid-5 of 7 breaths averaged using the Ultima CardiO2 gas exchange analysis system metabolic cart (MGC Diagnostics). A fitted air-cushioned face mask (preVent) and a bidirectional breath-by-breath volume sensor (preVent) will be used to collect the ventilatory variables. The Ultima CardiO2 will be calibrated before each test by using automated gas and flow calibrations as well as quality assurance to ensure compliance with the procedures recommended by the ATS/ERS pulmonary function acceptability and repeatability guidelines, as described in the user manual. Heart rate will be recorded using a 12-lead Mortara electrocardiogram (ECG) embedded in the Ultima CardiO2 system [48]. Blood pressure will be recorded every 2 minutes using the Tango M2 Stress Test Monitor (SunTech Medical) system during the exercise test.

NIRS is a noninvasive optical technology that provides information on microvascular oxygen delivery and local tissue utilization in skeletal muscle during exercise [49,50]. This technology provides insight into the concentration and oxygenation of biological tissues through the status of light-absorbing chromophores, such as hemoglobin (Hb) and myoglobin (Mb) within the near-infrared region (700‐900 nm) penetrating several millimeters [25]. The NIRS device (PortaMon, Artinis Inc) will be placed on the vastus lateralis muscle [51-53], about 12‐14 cm above the knee, secured by a band to minimize motion artifacts during cycling exercise. Adipose tissue thickness will be measured over the vastus lateralis site using Sonosite PX Ultrasound System (FUJIFILM Sonosite, Inc).

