### Data Analysis

Similar to the $\dot{V}O_{2}$ analysis conducted on healthy adult populations [28], $\dot{V}O_{2}$ on-kinetics (rest-to-exercise transition), $\dot{V}O_{2peak}$, and $\dot{V}O_{2}$ off-kinetics (exercise-to-recovery transition) will be analyzed in the ICU-CARE CPET within a single bout—reporting the measured and predicted $\dot{V}O_{2peak}$ (mL kg^−1^ min^−1^), measured SS $\dot{V}O_{2}$ at CWR (mL kg^−1^ min^−1^), “actual” calculated 30% $\dot{V}O_{2reserve}$ (mL kg^−1^ min^−1^), and targeted intensity achieved at CWR as a percentage (%). Additionally, NIRS will be analyzed to evaluate skeletal muscle microvascular oxygenation. The primary variables will be pulmonary $\dot{V}O_{2}$, deoxyhemoglobin (HHb; deoxy[Hb+ Mb]), and TSI ($\frac{\left[oxy\left(Hb+Mb\right)\right]}{\left[oxy\left(Hb+Mb\right)\right]+\left[deoxy\left(Hb+Mb\right)\right]}*100$), measured noninvasively at a sample rate of 10 Hz.

Skeletal muscle oxygenation measured by NIRS (Portamon, Artinis Medical Systems) will be transmitted wirelessly into OxySoft software, time-synched with the metabolic cart with real-time impulse by inserting key commands on the NIRS computer (listed in Figure 1). On OxySoft, export NIRS data to Microsoft Excel, then adjust to timestamps as described above and illustrated in Figure 2. For a combined analysis, $\dot{V}O_{2}$ and NIRS data will be preprocessed using a customized LabVIEW code (LabView v20.0.01, National Instruments Corp), specifically designed to perform the required analyses. The first analysis removes noise and motion artifacts. Initially, outliers will be removed by applying 2 standard deviations in a window size of 7 seconds, then applying a 350-second moving average, linearly interpolated to provide second-by-second values [52]. Then, the data is resampled at 1 Hz and time-aligned with each transition to be synchronized with the metabolic cart.

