With exercise starting at zero, subsequent analysis will be performed using a mono-exponential model to fit the pulmonary or primary component of the $\dot{V}O_{2}$ response (ie, phase II) by skipping the cardiogenic phase (ie, phase I), as previously recommended [33,58], left-shifting at 20 s in length [52]. Then, the steady-state $\dot{V}O_{2}$ (SS $\dot{V}O_{2}$ or phase III) will be calculated as the average of the last 2 minutes of the CWR exercise phase [28]. The mono-exponential fitting is characterized by $\dot{V}O_{2}$ parameters, including tau (τ), time delay (TD), amplitude A_0_ and A_1_, and mean response time (MRT), where τ is defined as the time constant of the exponential function, representing the time taken to reach 63% of the steady-state or final value; TD records the delay to the exponential response start (ie, phase II) (the model is not constrained to pass through the origin) before oxygen uptake responds to exercise; A_0_ represents the baseline value (resting $\dot{V}O_{2}$), whereas A_1_ represents the change of amplitude from baseline to steady-state $\dot{V}O_{2}$ (ie, SS $\dot{V}O_{2}$ – baseline value); and MRT, defined as TD + τ, representing the overall time to adjust the rate of $\dot{V}O_{2}$ to changes in workload [28]. At the end of the incremental phase, $\dot{V}O_{2peak}$ will be defined as the highest value of the last 30 seconds before volitional exhaustion after applying a 20-second moving average [59,60]. The quality of the fitting will follow our previous protocol [28]. The analysis of residuals, the degree of linear correlation between the experimental data and fitted function (*r*), the 95% CI band, and the significance level (*P* value) of the estimated parameters are used to determine the quality of the fitting.

The HHb signal will be normalized using a 60-second average before the exercise begins, then analyzed by detecting the nadir, occurring after a sudden decrease in HHb signal, to exclude data not associated with muscular $\dot{V}O_{2}$ dynamics, referring to the muscle pump [61]. After the nadir, HHb increases monoexponentially, representing the $\dot{V}O_{2}$ dynamics during the onset of exercise [27,62-64].

The HHb monoexponential function is expressed in the equation below:

$$HHb\;{\left(t\right)}^{\;}=HHb_{bl}+a\left[1-e^{-\left(t-TD\right)/\tau }\right]$$

where HHb_bl_=HHb baseline, *a*=amplitude, *e*=mathematical constant, *t*=time, TD=time delay, and τ=time constant.

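### VO2 kinetics appear to be fitted to a mid-5-of-7-breath average with no stated time-stamp; if values are stamped at the last breath, mean response time is about three breaths too long

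*Protocol article*

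**What the plan says.** Under Equipment, the cart's VO2, VCO2 and their ratio "will be collected, monitored, and reported mid-5 of 7 breaths averaged". The same paragraph adds that "a bidirectional breath-by-breath volume sensor (preVent) will be used to collect the ventilatory variables". So the hardware resolves single breaths, but the series described as collected is an average over seven.

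Under Data Analysis, pulmonary VO2, deoxyhemoglobin (HHb) and tissue saturation index are listed together as "measured noninvasively at a sample rate of 10 Hz". VO2 and NIRS data then go through one shared chain. It begins with a 2-SD outlier filter over 7-second windows. The smoothing step is worded as "then applying a 350-second moving average, linearly interpolated to provide second-by-second values". In the last step of the chain, "the data is resampled at 1 Hz and time-aligned with each transition to be synchronized with the metabolic cart".

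The mono-exponential fit skips the first 20 s as phase I and leaves TD free. The summary measure is given as "MRT, defined as TD + τ, representing the overall time to adjust the rate of" oxygen uptake when the load changes. The constant-work-rate phase lasts 5 minutes. No section says that unaveraged breaths are exported for the fits, at which breath an average is time-stamped, or that any lag is corrected.

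**The concern.** A rolling seven-breath average suits a live display but not a kinetics fit. Seven breaths take 7 × 60/f seconds at f breaths/min: 26 s at 16/min and 15 s at 28/min. That is about as long as the 20 s skipped for phase I, so early points treated as phase II can still contain rest and phase I breaths. If the value is stamped at the last breath, the whole response is also displaced later by about half the window.

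The displacement depends on breathing rate, so it does not cancel. It can differ between participants, and between the on-transition, which starts from rest, and the off-transition, which starts from peak exercise. VO2 kinetics would look slower for a reason that is not metabolic, and breathing pattern would enter any later comparison with other populations, a use that the article anticipates.

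**Working it through.** **Which series is fitted.** The plan gives no lag, tau or MRT value to reproduce. Setting Equipment beside Data Analysis, VO2 cannot be both a seven-breath average and a 10 Hz measurement. At 20 breaths/min there are 20 new values a minute, against 600 at 10 Hz. Single breaths do not fit 10 Hz either, so that wording does not settle which series is used.

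**Lag by arithmetic.** The central breath of seven lies three breaths before the last. With a last-breath stamp, lag ≈ 3 × 60/f = 180/f s.

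**Simulation.**
- From the plan: mid-5-of-7 average; 1-s interpolation; fit from 20 s over a 300-s phase; amplitude, TD and tau free; MRT = TD + tau.
- Assumed, because the plan gives no values: rolling window with the highest and lowest breath dropped; baseline 0.3 and amplitude 0.5 L/min; TD 20 s; tau 30, 45 and 60 s; steady breathing.
- The 350-s moving average is left out (see the last paragraph of this section).
- Bias = fit to the averaged series minus the same fit to unaveraged breaths.

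Last-breath stamp, fit from 20 s:

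| Breaths/min | 180/f (s) | MRT bias (s) | Tau bias (s) |
|---|---|---|---|
| 15 | 12.0 | +14.1 to +15.7 | +7.5 to +8.0 |
| 20 | 9.0 | +10.3 to +11.2 | +4.7 to +5.0 |
| 30 | 6.0 | +6.7 to +7.0 | +2.5 to +2.7 |
| 40 | 4.5 | about +5 | +1 to +2 |

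Added noise (SD 0.05) gave similar results.

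**Rising breathing rate.** With 20% of the amplitude in a 20-s phase I and true tau of 25, 40 and 60 s:
- 16 rising to 22/min: MRT goes from 39.4 to 48.6, 51.1 to 60.4 and 66.6 to 76.3 s, that is +9.2, +9.3 and +9.7 s; tau +5.1, +4.2 and +3.9 s.
- 20 rising to 28/min: MRT +7.2 to +7.5 s; tau +2.4 to +3.5 s.

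**Which part is robust.**
- Fit from 40 s or later, 12 to 40 breaths/min: tau bias 0.0 to +0.5 s, MRT still +4.5 to +15.8 s. The lag moves into TD.
- TD 10 s, tau 40 s, fit from 20 s, 15 to 30 breaths/min: tau 0.0 to +1.8 s, MRT +6.1 to +12.7 s.
- TD 25 s, same settings: tau +4.4 to +10.3 s, MRT +7.5 to +15.8 s.

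The MRT shift is present throughout. The tau shift depends on where phase II starts relative to the 20-s fit start.

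**Centre-breath stamp.** At 15 to 30 breaths/min, fit from 20 s: tau +0.3 to +1.2 s, MRT +0.2 to +0.6 s.

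**Spread from breathing rate alone.** Two transitions with steady rates of 15 and 30/min would differ by 12.0 − 6.0 = 6 s in lag. Only the on-transition was simulated; for the off-transition the 180/f rule is carried over.

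**Relation to the 350-s moving average.** Taken literally, that step is longer than the 300-s phase and gives a fitted tau of 366 to 587 s for true values of 30 to 60 s, even from unaveraged breaths. It is a separate and larger problem, and correcting it leaves this one in place.

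**The case against.** The strongest reply is that the harm turns on a fact the plan does not give. With a centre stamp almost nothing is lost, so the result runs from negligible to 10 s or more on an export setting. That stands, and the size is conditional on it.

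It can also be said that the averaging sentence sits under Equipment, that the same paragraph names a breath-by-breath sensor, and that outlier removal and interpolation work equally well on raw breaths. So it is an inference, though the natural one, that the averaged series is fitted. The inference is fair because the article sets out the processing chain in detail, describes the average as what is collected, and never returns to single breaths.

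Three stronger readings are tempting, and the document does not support them:
- **That the plan sets averaged VO2 against HHb at 10 Hz.** The 10 Hz phrase covers VO2, HHb and tissue saturation together, both signals share the later smoothing, and no test of VO2 timing against HHb timing is specified.
- **That tau is always too slow.** A free TD can absorb most of a pure lag.
- **That VO2peak is affected.** No such error has been shown.

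Finally, the primary outcome is feasibility, the sample size rests on VO2peak agreement, and kinetics are secondary physiological observations summarised descriptively. That limits the weight of the point but does not remove it, since measuring on/off kinetics is one of the protocol's stated aims.

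**Conclusion.** The point holds in conditional form. As written, the plan most naturally feeds a seven-breath average into the kinetics fits, gives no time-stamp, and describes VO2 sampling in two incompatible ways. If values are stamped at the last breath, TD and MRT are too long by about three breaths or slightly more. In the rising-rate simulations, with true tau of 25 to 60 s, that was 11% (7.5/66.6) to 23% (9.2/39.4) of MRT. Tau inflation is a secondary effect that needs phase II to begin near the 20-s fit start. Breathing rates, tau, TD and the rolling form of the average are assumptions. The feasibility outcome, the sample size and VO2peak are untouched. The change should be made because it is cheap and, on the stated timeline, recruitment starts only in June 2026.

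**What to change.** - State that on- and off-kinetics are fitted to unaveraged breath-by-breath VO2 exported from the cart, cleaned of errant breaths and interpolated to 1 Hz.
- Restrict the mid-5-of-7 average to monitoring and the printout.
- Correct the 10 Hz wording so that it applies to NIRS only.
- If averaged data must be kept for the fits, stamp each value at its central breath and say so.
- Give the breath-cleaning rule for VO2 separately: a 7-second window holds only about 7 × 20/60 = 2.3 breaths at 20/min, too few for a 2-SD rule.

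The cost is an export setting and a few sentences. Single-bout fits to raw breaths will be noisier, with wider confidence intervals. The earlier healthy-adult data should be processed in the same way before any comparison. No change to the VO2peak derivation is needed on this ground.
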